## Abstract

**Background:**

1.2 million children under 15 years are estimated to have developed tuberculosis (TB) in 2021. 85% of paediatric patients achieve successful treatment outcomes if treated for the first episode of TB. However, despite so-called successful treatment, TB leaves many survivors with permanently destroyed or damaged lungs. Data from prospective paediatric cohorts to establish the burden and evolution of post-TB lung disease (PTLD) are still absent. The *Childhood TB Sequel* study aims to describe respiratory consequences associated with pulmonary TB in Gambian children, describe the evolution of these sequelae, and determine associated epidemiological risk factors.

**Methods:**

We aim to recruit up to 80 subjects aged 19 years and below who have recently completed treatment for pulmonary TB. Recruitment started in April 2022 and is expected to continue until June 2024. Clinical assessment, chest X-ray, and comprehensive lung function assessment are carried out at treatment completion and again six and 12 months later.

**Discussion:**

The *Childhood TB Sequel* study will address existing research gaps to enhance our knowledge and understanding of the burden of PTLD in Gambian children. The study will also contribute to formulating a plan for post-TB evaluation and long-term follow-up strategies.

**Trial registration:**

ClinicalTrials.gov: NCT05325125, April 13, 2022.

## Background

In 2021, an estimated 10.6 million people fell ill with tuberculosis (TB), of which 1.2 million were children under 15 years [1]. Approximately 80% of these childhood TB cases affect the lungs [1]. However, from an optimistic standpoint, more than 85% of persons who receive treatment for the first episode of TB have a successful outcome, defined as smear or culture conversion to negative or clinical improvement on anti-tubercular treatment [1]. This success in treatment has resulted in about 155 million TB survivors as of 2020, of which 12% were children below 15 years of age [2].

The care for patients diagnosed with TB often ends at treatment completion without any further consultations to evaluate their health and well-being [3]. However, even after successful treatment, which is traditionally classified as either ‘cured’ or ‘treatment completed’, [4] pulmonary TB could permanently destroy or damage the lungs and progress from a treatable communicable disease into a chronic, non-communicable illness across the life course [5]. Moreso, there is increasing evidence that TB survivors continue to experience long-term sequelae that impact their physical and mental health, households, and communities even after successful treatment [5].

Although a growing literature describes a wide range of post-TB sequelae in adults, the actual burden and spectrum of post-TB lung disease (PTLD) remain poorly described in children. Our group previously documented that 52% of childhood TB survivors continued to experience recurrent respiratory symptoms beyond six months after treatment completion [6]. We also reported significantly reduced lung volumes and health-related quality of life in the childhood TB survivors compared to a healthy comparison group. Similarly, a prospective cohort study in Cape Town, which followed children from birth until five years of age, found that children who developed TB were more likely to wheeze consistently and had reduced anthropometry and lung function parameters in the post-TB period compared to children who never had TB [7].

The impact of TB on the lungs of children may be subclinical. Hence more detailed prospective paediatric data using lung function measurements regardless of symptoms and social determinants for lung health are urgently needed to establish the burden and evolution of PTLD in children [8]. The *Childhood TB Sequel* study seeks to add to the growing body of evidence by generating data describing respiratory symptoms, radiological abnormalities and lung function impairment in children after completing pulmonary TB treatment in The Gambia. The study will also assess how abnormalities evolve over the period of 12 months after treatment completion. This study includes adolescents aged 15 to 19 who have a considerably high incidence of TB and are often neglected in childhood TB research [9].

## Methods/design

### Study aims

The *Childhood TB Sequel* study aims to measure the proportion of Gambian children with long-term adverse outcomes associated with pulmonary TB, to describe the evolution of these sequelae, and to determine the epidemiological risk factors associated with these sequelae.

### Study setting

This study is set in the Greater Banjul Area (GBA) of The Gambia, which has mixed urban, peri-urban and rural populations [10]. In 2021, the incidence of TB in The Gambia was estimated to be 149 per 100,000 population [1]. Over 70% of all cases of TB notified in the country reside in the GBA [11]. Children aged 19 years and below comprise about 15% of all notified TB cases annually [1, 12].

After receiving a diagnosis of bacteriologically confirmed or clinically diagnosed (unconfirmed) pulmonary TB by public or private health providers, individuals are referred to their preferred Gambia National Leprosy and Tuberculosis Programme (NLTP) treatment clinic. The treatment clinics in different parts of the country are run by designated Leprosy and Tuberculosis Inspectors (LTI) who provide TB treatment, monitor treatment adherence, and assess the outcome at treatment completion. There are 20 TB treatment clinics in the GBA, which serve a population of about 700,000 [13].

### Study design and participant eligibility

The *Childhood TB Sequel* is an ongoing prospective cohort study in the GBA of The Gambia. Children aged 19 years and below who are in the final month of their treatment for pulmonary TB at any of the NLTP treatment clinics in the GBA are identified for possible inclusion in the study. After treatment completion and outcome classification by the LTI, each study participant is eligible if they meet all of the inclusion criteria and none of the exclusion criteria summarised in Table 1.

**Table 1 Tab1:** Inclusion and exclusion criteria

Inclusion criteria	Exclusion criteria
Aged 19 years and below on the date of treatment completion	Relocate from the study area during the follow-up period
Residing within the Greater Banjul Area	Develop recurrent* pulmonary TB during the follow-up period
Previously diagnosed with either confirmed or unconfirmed pulmonary TB	
Have completed treatment with an outcome of *cured* or *treatment completed* within the preceding six weeks	
For children below 18 years, parent/caregiver willing to provide written informed consent as well as assent	

*either a true relapse or a new episode of TB caused by reinfection [4]

### Recruitment and procedures

Recruitment commenced in April 2022 and is expected to continue until June 2024. The study duration is 12 months, comprising an initial baseline (enrolment) visit and two follow-up time points at six months and 12 months from the enrolment date. A symptom screening will also be conducted via telephone at three and nine months. Table 2 shows the study time points and schedule of events (SOE). We aim to follow-up all children from baseline up to 12 months, regardless of their respiratory function.

We will evaluate clinical, radiological, spirometry and functional capacity measurements during the study visits according to the SOE in Table 2. Finally, we will characterise the changes in lung function over a period of 12 months after treatment completion.

**Table 2 Tab2:** Schedule of Events (SOE)

	Baseline	Month 3^#^	Month 6	Month 9^#^	Month 12	Unscheduled visit
Current symptoms	X	X	X	X	X	X
Clinical assessment	X		X		X	X
Anthropometry	X		X		X	X
Physical examination	X		X		X	X
Chest x-ray	X		X		X	ICI
Spirometry	X		X		X	ICI
6-minute walk test	X		X		X	
Respiratory sample* for Xpert MTB/RIF Ultra	ICI		ICI		ICI	ICI

* Sputum (spontaneous or induced)/nasogastric aspirate

^#^ Conducted via telephone call

ICI: if clinically indicated

#### Clinical assessment

During the enrolment visit, we will obtain relevant clinical information, which will include current self- or parent-reported symptoms derived from the St George’s Respiratory Questionnaire, [14] a detailed history of the recent episode of TB for which they have just completed treatment, previous TB history, history of other known illnesses, smoking history and environmental exposure to smoking and biomass fuel. Additionally, we will conduct a general physical examination, nutritional assessment using anthropometric measurements, and detailed respiratory examination at enrolment, at six months and 12 months.

#### Radiological assessment

Per the SOE, we will obtain a chest X-ray (CXR) for each subject at enrolment, six months, and 12 months. Where available, radiographs obtained at TB diagnosis will also be reviewed and assessed for the classification of severity of TB disease as per the radiological case definitions [15]. The radiographs will be interpreted by two independent clinicians experienced in paediatric TB. A third reader will be used to resolve discrepancies in cases where there is a disagreement.

The radiological features of paediatric pulmonary TB are different from adults. In children, the disease is less likely to cause lung cavities commonly seen in adults and adolescents [16]. We expect the severity and typical patterns of post-TB radiological features to vary widely and to be related to the age and the radiological extent of the disease at diagnosis.

#### Lung function measurement

Lung function assessment will be performed for all children above four years by a trained technician using an Easy on-PC portable spirometer (ndd Medical Technologies, Zurich, Switzerland). Spirometry will be performed according to the American Thoracic Society (ATS)/European Respiratory Society (ERS) guidelines [17]. Briefly, we will record the ambient temperature, humidity and altitude prior to daily data collection. Subsequently, the spirometer will be calibrated using a 3 L syringe to ensure that measured volumes are within 3% of the syringe volume. After assessing for contraindications, we will explain and demonstrate the procedure. We will then ask the participant to perform up to eight forced exhalations while sitting. The procedure is repeated for all participants after receiving a bronchodilator (BD), salbutamol, via a spacer device.

Two reviewers will independently assess each spirogram for acceptability and repeatability and agree on a consensus result where there is discordance. Only spirometry traces that meet the ATS quality criteria will be included in the analysis. We will then record the z-scores for the highest forced vital capacity (FVC) and forced expiratory volume in 1 s (FEV1) and use this for the analysis. The Global Lung Function Initiative (GLI) 2012 reference equations will be used as the reference standard for spirometry data analysis, where FEV1, FVC or FEV1/FVC ratio below the lower limit of normal (LLN) will be deemed abnormal for the participants (Table 3) [18].

#### Functional capacity measurement

The six-minute walk test (6MWT) is a standardised measure of functional capacity or changes in functional capacity due to intervention in patients with lung disease [19]. The 6MWT will be assessed for all children above four years at the baseline, month 6, and month 12 study visits. The 6MWT will be performed according to the ATS guidelines [19]. In brief, the test will be conducted along a 30-meter-long, flat corridor with marked distances and turnaround points. Before starting the test, the participant will be requested to sit and rest for at least 10 min. After recording the baseline vital signs, dyspnoea and fatigue level will be documented using the Borg scale [20]. Afterwards, we will ask the participant to walk back and forth around the turnaround points. The objective is for the participant to walk as far as possible for six minutes, exerting themselves and taking rests as needed. At the end of six minutes, we will record the distance (in meters) covered by the participant, vital signs and fatigue level.

### Outcomes and case definition

The primary outcome for this study is PTLD at enrolment, at six months and 12 months after enrolment. Post-TB lung disease, as proposed during the first international post-tuberculosis symposium, will be operationally defined as *“evidence of chronic respiratory impairment in an individual previously adequately treated for pulmonary tuberculosis in whom active tuberculosis is excluded and in whom no other cause of chronic lung disease is the predominant cause”.* [5].

Evidence of chronic respiratory impairment will be assessed using self- or parent-reported chronic or recurrent respiratory symptoms derived from the St George’s Respiratory Questionnaire, [14] lung function measured by spirometry, and CXR occurring alone or in combination (Table 3). The evolution and pattern of change over the 6-monthly intervals will be assessed and classified as ‘improvement’, ‘no change’ or ‘deterioration’ based on pre-defined minimum clinically important difference (MCID) cut-offs for the measured parameters.

**Table 3 Tab3:** Post-TB lung disease measurement parameters

Parameter	Abnormality signifying PTLD
Self- or parent-reported chronic or recurrent symptoms	Presence of any symptom
Lung function	*z*-score below the lower limit of normal (-1.64)
• Forced vital capacity (FVC) • Forced expiratory volume in 1 s (FEV1) • FEV1/FVC	
Chest X-ray	Presence of any TB-related abnormalities

**PTLD: post-TB lung disease*

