### Sample size

Over the past five years, the annual average notification of childhood and adolescent pulmonary TB in the GBA of The Gambia is 90. Assuming a population prevalence of the primary outcome, abnormal lung function, of 38.5%,^6^ and a finite population size of 90, a sample size of 73 cases allows the estimation of the proportion of children who develop post-TB lung function impairment in one year with 95% confidence and a margin of error of less than 5%. To allow for attrition, we will aim to enrol at least 80 children and adolescents. We expect at least 28% of all enrolled children to have had microbiologically confirmed TB [21]. We aim to follow-up all children from baseline up to 12 months, regardless of their respiratory function.

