### Statistical analysis

The burden of children with the primary outcome, abnormal lung function, at baseline, at six months and 12 months after pulmonary TB treatment completion will be estimated (along with the corresponding 95% confidence interval) overall and stratified by confirmed versus unconfirmed pulmonary TB sub-groups. A pairwise comparison between the baseline and 6-month data and between the baseline and 12-month data will be made using McNemar’s test for categorical variables and the sign rank test for continuous variables. Linear mixed effects and logistic models will be used to estimate predictors of abnormal lung function over time. The impact and form of influence of the variables will be explored graphically and by calculating proportions or quantiles depending on the nature of the data.

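### The outcomes section makes composite PTLD the primary outcome, while the sample size and analysis sections give that title to abnormal lung function alone

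*Protocol article*

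**What the plan says.** Three sections of the protocol article use the term primary outcome, and they do not agree.

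- **Outcomes and case definition:** "The primary outcome for this study is PTLD at enrolment, at six months and 12 months after enrolment". Respiratory impairment may be shown by reported symptoms, by spirometry or by chest X-ray, singly or together. Table 3 sets low thresholds: "Presence of any symptom" for symptoms, FVC, FEV1 or FEV1/FVC below a z-score of -1.64 for lung function, and "Presence of any TB-related abnormalities" for chest X-ray. The definition also requires that active TB be excluded and that no other cause of chronic lung disease predominate.
- **Sample size:** "Assuming a population prevalence of the primary outcome, abnormal lung function", put at 38.5%. The stated target is the proportion of children who develop lung function impairment in one year.
- **Statistical analysis:** "The burden of children with the primary outcome, abnormal lung function, at baseline, at six months and 12 months" is to be estimated with a 95% confidence interval, overall and by confirmed or unconfirmed TB. The predictor models are also for abnormal lung function.

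The Discussion returns to PTLD and says that its proportion will be measured at all three visits. No section ranks the two outcomes or calls either of them secondary.

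**The concern.** The main product of this cohort is a prevalence, so the reader must be able to tell which prevalence is the main result. As written, the declared primary outcome (PTLD) has no named estimate or model in the analysis section, and the outcome that is sized and analysed is one of its components. Either could be presented as the primary result, and the choice could be made after both are known.

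The two are not interchangeable. A child with normal spirometry and a single recurrent symptom can count under one and not under the other. They also cover different children. Under Lung function measurement, spirometry is limited to children above four years, and only traces meeting ATS quality criteria are analysed. Table 1 admits anyone aged 19 years and below, and symptoms and chest X-ray carry no lower age limit.

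**Working it through.** **1. Which outcome each planned element serves**

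| Element | Section | Outcome named |
|---|---|---|
| Declaration of primary outcome | Outcomes and case definition | PTLD (composite) |
| Assumed prevalence 38.5%, n = 73 | Sample size | Abnormal lung function |
| Burden with 95% CI, overall and stratified | Statistical analysis | Abnormal lung function |
| McNemar and signed rank comparisons | Statistical analysis | None named |
| Mixed effects and logistic models | Statistical analysis | Abnormal lung function |
| Proportion at three time points | Discussion | PTLD |

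**2. Reproducing the stated sample size**

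Inputs from the Sample size section: p = 0.385, margin d = 0.05, 95% confidence (z = 1.96), finite population N = 90.

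- n0 = z² p(1 - p) / d² = 1.96² × 0.385 × 0.615 / 0.05² = 363.8
- n = n0 / (1 + (n0 - 1)/N) = 363.8 / (1 + 362.8/90) = 72.3, rounded up to **73**
- Margin at n = 73: 1.96 × √(0.385 × 0.615/73) × √((90 - 73)/(90 - 1)) = 0.0488, below 5% as stated

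The figure of 73 is reproduced, from an input that belongs to abnormal lung function.

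**3. How far apart the two prevalences could be**

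The protocol gives no prevalence for composite PTLD. It does give two component rates, both cited to the same earlier study by the group: 38.5% for abnormal lung function (Sample size) and, in the Background, "52% of childhood TB survivors continued to experience recurrent respiratory symptoms beyond six months after treatment completion". *Assuming* both rates apply to this cohort, and before excluding other causes of lung disease, the proportion with symptoms or abnormal lung function is:

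- full overlap (the minimum): max(0.385, 0.52) = 52%
- independence: 1 - (1 - 0.385)(1 - 0.52) = 1 - 0.615 × 0.48 = 70.5%
- no overlap (the maximum): 0.385 + 0.52 = 90.5%

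Adding chest X-ray can only raise these. With an assumed chest X-ray abnormality rate of 10% to 50%, and independence, the result is 1 - 0.615 × 0.48 × 0.90 = 73.4% to 1 - 0.615 × 0.48 × 0.50 = 85.2%.

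The gap from 38.5% is therefore at least 52 - 38.5 = 13.5 points, and 70.5 - 38.5 = 32 points under independence. The planned margin of error is under 5 points.

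**4. Whether the sample would still suffice for PTLD**

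Same formula, N = 90 and d = 0.05, with the composite prevalence varied:

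| Prevalence | n unrounded | n required |
|---|---|---|
| 52% | 73.05 | 74 |
| 60% | 72.5 | 73 |
| 70.5% | 70.4 | 71 |
| 80% | 66.1 | 67 |
| 90% | 54.8 | 55 |

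All are below the 80 children to be enrolled. The largest exceeds the stated 73 by one child.

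**The case against.** The strongest defence is that this is a descriptive cohort, that every component is measured at every visit, and that both prevalences will probably be reported. The comparison tests are worded for categorical and continuous variables in general and could be applied to PTLD, and the Discussion promises the PTLD proportion. All of that is fair. It would be wrong to say that PTLD will go unanalysed; what can be said is that the analysis section names no estimate or model of it. The defence does not remove the contradiction. Condensation for a journal, or a statistical analysis plan that is not shown, could explain missing detail but not two different outcomes each called primary in current text.

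Four stronger readings are tempting, and the documents do not support them:

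- **The sample is too small for PTLD.** The calculation above shows otherwise on the protocol's own formula and population.
- **Impairment developing within a year cannot be estimated.** Without pre-TB spirometry, onset relative to the pre-TB state cannot be, but new impairment among children normal at baseline could be. The wording may also be a loose way of saying prevalence, since the 38.5% input is itself called one. It is imprecise and does not match the analysis section; that is all.
- **A single primary visit must be named.** The outcomes and analysis sections agree on the same three visits and treat them equally. For a study meant to describe evolution, choosing one visit is a preference.
- **The two results may differ by 50 points or more.** That requires no overlap at all between symptoms and abnormal spirometry, which is implausible.

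**Conclusion.** The contradiction is established from the text alone and depends on no calculation: the outcomes section names composite PTLD as primary, and the sample size and analysis sections name abnormal lung function. Followed as written, the plan leaves its declared primary outcome without a named estimate or model.

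The size of the consequence is conditional. A difference of 13.5 points or more, and about 32 points under independence, rests on carrying the earlier 38.5% and 52% rates into this cohort. The 52% was observed beyond six months after treatment, so it may not hold at enrolment. PTLD also excludes active TB and disease mainly due to other causes, so 52% is not a guaranteed floor for PTLD itself. A clear difference is plausible; its exact size cannot be derived from the documents. What is at stake is which quantity the study reports as its main result and in which children. The adequacy of the planned 80 is not in question on this point, taking the protocol's finite population of 90 as given.

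**What to change.** Use one primary outcome in the Outcomes, Sample size and Statistical analysis sections, label the other secondary, and state the denominator of each.

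- **If abnormal lung function is primary:** say so in the Outcomes section, and define it for children above four years with spirometry that meets the quality criteria.
- **If PTLD is primary:** restate the assumed prevalence and precision for the composite, and name PTLD in the burden estimate and the models. Say how PTLD is classified in children who have no usable spirometry.

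In either case, replace the Sample size wording about children who develop impairment in one year with the quantity that the analysis section estimates, namely prevalence at each visit.

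The cost is wording in the protocol and, where one exists, the statistical analysis plan. No new data, visits or participants are needed. The choice should be recorded before results are examined.

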### Sample size

Over the past five years, the annual average notification of childhood and adolescent pulmonary TB in the GBA of The Gambia is 90. Assuming a population prevalence of the primary outcome, abnormal lung function, of 38.5%,^6^ and a finite population size of 90, a sample size of 73 cases allows the estimation of the proportion of children who develop post-TB lung function impairment in one year with 95% confidence and a margin of error of less than 5%. To allow for attrition, we will aim to enrol at least 80 children and adolescents. We expect at least 28% of all enrolled children to have had microbiologically confirmed TB [21]. We aim to follow-up all children from baseline up to 12 months, regardless of their respiratory function.

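### The stated margin of error below 5 points rests on treating one year's 90 notifications as the whole population; 73 evaluable children give about ±8.5 to ±11 points, depending on the target population

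*Protocol article*

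**What the plan says.** The Sample size section starts from the notification count over the past five years: "the annual average notification of childhood and adolescent pulmonary TB in the GBA of The Gambia is 90". It then sets the expected proportion ("Assuming a population prevalence of the primary outcome, abnormal lung function, of 38.5"%), and uses the 90 as the population: "finite population size of 90, a sample size of 73 cases allows the estimation of the proportion of children who develop" impaired lung function. The precision claimed for the 73 is "with 95% confidence and a margin of error of less than 5"%. The target is then raised: "To allow for attrition, we will aim to enrol at least 80 children and adolescents".

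Two other sections bear on whether 90 is the right population. Under Recruitment and procedures: "Recruitment commenced in April 2022 and is expected to continue until June 2024". Under Study aims, the study "aims to measure the proportion of Gambian children with long-term adverse outcomes associated with pulmonary TB", and it is also to describe how the sequelae evolve and which risk factors go with them.

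The Statistical analysis section plans a 95% confidence interval for the proportion with abnormal lung function at each time point. It does not name an interval method.

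**The concern.** A finite-population correction shrinks the standard error because the sample uses up most of a fixed, listed population, and that list is the only thing about which a statement is made. With 73 out of 90, little is left unobserved, so the margin looks small. This is legitimate only if the 90 are both the pool from which children are drawn and the full target of inference.

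Here neither seems to hold. The 90 is a count per year, while enrolment lasts more than two years. The aim, and the Discussion's intention to inform long-term follow-up strategy, point beyond the children notified in any one year.

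The prevalence with its interval is the first analysis that the plan lists, and this paragraph is its only sample-size justification. A reader or funder is told to expect an estimate good to under 5 points, when the design gives roughly twice that uncertainty. If the N = 90 correction were also carried into the analysis, the published interval would be too narrow.

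**Working it through.** **Inputs**

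- Expected proportion p = 0.385, population N = 90 (one year's average notifications), margin d = 0.05 (read as percentage points, the reading that reproduces 73), 95% confidence so z = 1.96: Sample size section.
- Recruitment April 2022 to June 2024, that is 26 to 27 months: Recruitment and procedures.
- Treatment success of about 85%: Abstract and Background. This is a general figure, used below only for a sensitivity reading.

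**Step 1: reproduce the plan's 73**

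- Uncorrected size: n0 = z² p(1−p)/d² = 1.96² × 0.385 × 0.615 / 0.05² = 363.8.
- Corrected size: n = n0 / (1 + (n0 − 1)/N) = 363.8 / (1 + 362.8/90) = 72.3, rounded up to 73. This matches the plan.
- Check of the margin: the uncorrected half-width at n = 73 is 1.96 × √(0.2368/73) = 0.1116. The correction factor is √((90 − 73)/89) = 0.437. The product is 0.0488, or 4.9 points, which is below 5 as stated.

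So the whole step from 11.2 to 4.9 points comes from the factor 0.437.

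**Step 2: the pool implied by the recruitment period**

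- 90 × 26/12 = 195 notifications; 90 × 27/12 = 202.5.
- If only the roughly 85% with a successful outcome can be enrolled: 0.85 × 202.5 = 172 (0.85 × 195 = 166).

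**Step 3: the half-width at n = 73 for each target**

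Half-width = 0.1116 × √((N − 73)/(N − 1)). The last column is n0 / (1 + (n0 − 1)/N), rounded up.

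| Target of inference | N | Factor | 95% half-width | n needed for 5 points |
|---|---|---|---|---|
| One year's notifications (as planned) | 90 | 0.437 | 4.9 points | 73 |
| Notifications in the window, 85% eligible, 27 months | 172 | 0.761 | 8.5 points | 118 |
| Notifications in the window, 26 months | 195 | 0.793 | 8.9 points | 128 |
| Notifications in the window, 27 months | 202.5 | 0.802 | 8.9 points | 131 |
| Wider or future population | no correction | 1 | 11.2 points | 364 |

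With 85% eligible and 26 months (N = 166) the half-width is 8.4 points, so that reading hardly moves.

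**Step 4: what a reader would see**

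- If 28 of 73 children were abnormal (38.4%), an ordinary Wilson interval would run from 28.1% to 49.8%, and the Clopper-Pearson interval from 27.2% to 50.5%.
- If all 80 enrolled children were evaluable, the uncorrected half-width would be 1.96 × √(0.2368/80) = 10.7 points.

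**The case against.** The strongest defence is that nothing is miscalculated or hidden. The section names the finite population, gives its size, and computes correctly from it. That stands: the fault lies in an assumption, and it would be wrong to call it an arithmetic error.

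A second defence is that the section speaks of impairment in one year, so that one year's cases might be the intended population. This does not rescue the figure. If the phrase means the 12-month follow-up, it does not limit the population. If it means one year's notified cases, it conflicts with the recruitment dates.

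A third defence is that ±11 points is only the least favourable reading. That also stands in part. If the target is confined to cases in the area during recruitment, a correction with the larger N is defensible and gives about ±8.5 to ±8.9. The stated aim favours the wider reading, but the range should be given.

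Two stronger inferences are tempting, and the documents do not support them.

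- **That the reported interval cannot match the planned one.** The Statistical analysis section names no method and neither includes nor rules out a correction. Interval construction may well be settled in an analysis plan that is not shown.
- **That 80 children cannot be enrolled because 90 × 0.85 is only about 76.** The 85% is a general background figure, which the Background gives as a lower bound; it is not a rate for the Greater Banjul Area. The 90 is itself an average, and the recruitment window exceeds a year. No recruitment problem follows.

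**Conclusion.** The precision claim is wrong as written. At a prevalence of 38.5% with 73 evaluable children, the 95% half-width is about ±11.2 points for the wider population that the aim describes, or about ±8.5 to ±8.9 points for cases in the area during the recruitment window. Both are well above the stated limit of 5.

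These figures rest on the plan's own prevalence, the normal approximation, a steady 90 notifications a year over 26 to 27 months and, for the lowest figure only, about 85% treatment success. They also take 73 children as evaluable for lung function. The Lung function measurement section tests only children above four years and analyses only traces that meet the quality criteria, so the evaluable number could be smaller. The documents do not give the size of that loss, and it is not estimated here.

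The consequence is a misleading statement of precision. No planned procedure or test is invalidated, and an ordinary interval in the final report would show the true uncertainty. Should the N = 90 correction be used in the analysis, the interval would be 0.44 times the uncorrected width, or about 0.55 times the width for the recruitment-window target (4.88/8.95).

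**What to change.** Keep the sample size. In the Sample size section, remove the correction with N = 90 and replace the precision sentence with wording such as: *73 children with evaluable spirometry give a 95% confidence interval of about ±11 percentage points around an assumed prevalence of 38.5%.* State alongside it that the prevalence intervals will be reported without a finite-population correction; the choice of interval method can stay with the analysis plan.

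If the investigators do want inference only to a closed group, they should define that group, justify it against the stated aim, and use an N that matches the recruitment window. The margin would then be about ±8.5 to ±8.9 points, still not below 5.

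The cost is wording only. The stated precision becomes less favourable, and no extra participants are needed.
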